## 9 Randomisation of NHS Trusts / Health Boards

The NCA will inform the CTRU, University of Leeds, when each baseline audit is complete and the audit database has been locked for analysis.

Trusts or Health Boards will be randomised by the CTRU using an automated randomisation system based at the CTRU. It will remain possible to participate in each topic until each baseline audit database has been locked.

Trusts or Health Boards that fulfil the eligibility criteria, have NHS Permissions to participate and have completed the baseline audit will be randomised on a 1:1:1:1 basis to receive one of four feedback interventions twice, once after each baseline audit.

A computer-generated minimisation programme incorporating a random element will be used to ensure intervention arms are balanced for the following cluster-level characteristics:

- Trust size. For each audit we will review the number of cases submitted to baseline audit per cluster and then break these down into tertiles (Large, Medium and Small); the final cutpoints used will then be reported. This data was provided by the NCA after the close of audit data collection.
- Regional Transfusion Committee (RTC): refer to Appendix C for details of the RTC

For the second randomisation to the haematology audit, an additional stratification factor will be used which will include the previous randomised allocation to the first trial.

Where Trusts or Health Boards merge following each randomisation they will continue to be regarded as separate and distinct clusters for intervention, data collection and analysis purposes. For clusters that merge between trials dependent upon review these will continue to be regarded as distinct clusters as well. This will be accounted for in a sensitivity analysis.

Following each randomisation, the CTRU will inform the NCA, the Chief Investigators and the intervention delivery team so that appropriate arrangements can be made to facilitate the development and the delivery of the feedback according to randomised allocation.

Other personnel involved in the trial will only be informed of intervention allocation if this is required to undertake their role associated with the trial. A log will be maintained of who is unblinded to what at specific points in the research process.

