### 3 Trial Summary

This protocol describes two linked cluster randomised, factorial, cross-sectional trials, each evaluating the effects of two different enhanced feedback interventions, 'enhanced feedback documents' and 'post feedback support' developed and piloted during the first phases of the AFFINITIE research programme. These feedback interventions will be embedded within the current national audit and feedback programme for transfusion. We will compare both interventions against the current standard methods of feedback within the national transfusion audit programme. Each trial will occur in the context of a different audit topic. The two targeted transfusion topics will be (i) patient blood management in surgery and (ii) red blood cell (RBC) and platelet transfusions in haematology patients. These audits will run sequentially. Randomisation will be at the level of hospital NHS trust or Health Board, with stratification for size (volume of blood transfusions) and region (Regional Transfusion Committee). Hospital NHS Trusts and Health Boards will be randomised following each baseline audit for the surgical and haematology patient audit trials respectively. The primary outcome for each topic will be the proportion of patients receiving a transfusion coded as unnecessary. Two cost-effectiveness analyses (one for each audit topic) will be conducted using data generated by the trials as inputs into decision analytic models.

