### **13.2.1 Screening and confirmation of eligibility**

The NCA will provide CTRU with screening data on all NHS Trusts / Health Boards in the UK and will include the following information:

- Name of NHS Trust / Health Board and individual hospitals
- Eligibility (i.e. perform procedures relevant to either audit topic) correct at the point of first approach by the NCA and interest in taking part in the audit
- Eligibility and interest in taking part in the cluster trial
- Trust and Health Board size (defined by volume of blood transfusions) to inform the stratification of the randomisation and the planned moderator analysis

Documented reasons for ineligibility or declining participation will be closely monitored by the trial team as part of a regular review of the recruitment process. Screening data will be collected and collated by the NCA and forwarded to the CTRU for inclusion in the trial dataset.

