## 16.3 Statistical analysis

### 16.3.1 General considerations

Statistical analysis is the responsibility of the CTRU Statisticians. The analysis plan outlined in Section 18.3 will be reviewed, and a detailed Statistical Analysis Plan (SAP) approved, before any formal analysis is undertaken. The SAP will be drafted in accordance with CTRU standard operating procedures (SOPs) and will be finalised and agreed by the trial and supervising statisticians, the Chief Investigator and other appropriate members of the research team. Any changes to the final approved SAP, and reasons for change, will be documented.

The proportion of missing data is anticipated to be non-trivial, making the handling of missing data an important issue for the analysis. Mechanisms for missing data on key variables will

be explored, with the proportion of missing data to be compared between intervention arms, and a multiple imputation model built covering the main analyses. As a sizeable proportion of patients are expected to be missing from the main analyses and the missing data predictable by known variables, the principal method for handling this will be multiple imputation under a Missing at Random (MAR) assumption. Sensitivity analyses will be carried out to assess the impact of the choice of imputation model and of assuming data are Missing Not at Random (MNAR), as appropriate.

As the primary clinical effectiveness analysis for each topic has a single primary outcome but two main treatment effects, 2-sided 2.5% significance levels will be used for these contrasts. Where results are subsequently combined when interpreting the treatment effect (e.g. across secondary outcomes), full consideration will be given to the family-wise error rate and further adjustments made for multiplicity, as appropriate.

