### **16.3.4 Primary endpoint analysis**

For each topic independently, the patient-level binary primary outcome of unnecessary transfusions 12 months following randomisation will be analysed using logistic regression, with a random intercept for trust/health board, adjusting for design factors (that is, trust size, regional transfusion committee, and trust-level proportion of unnecessary transfusions at baseline), with contrasts for (1) enhanced vs. standard documents, (2) post-feedback support vs. no post-feedback support, and (3) the interaction between (1) and (2).

Unadjusted and adjusted intra-cluster correlations (ICCs) and corresponding 95% confidence intervals will be presented. We will report the estimates and two-sided 97.5% confidence intervals for the two main effects from this model.

In addition to sensitivity analyses relating to assumptions about the missing data mechanism we will also analyse the supportive outcomes that include a grey-area category using ordinal logistic regressions and look for consistency in the size, direction and interpretation of effect.

Following the analysis of each topic independently, a further analysis will be conducted using data from both audit topics. This analysis uses a bivariate patient-level binary primary endpoint outcome of unnecessary transfusions 12 months following randomisation and will be analysed using multivariate logistic regression, with a random intercept for trust/health board and will be adjusted for the same design factors as above and additionally controlled for audit topic. The model will then include contrasts for (1) enhanced vs. standard documents, (2) post-feedback support vs. no post-feedback support and (3) the interaction between (1) and (2). We will then fit all possible interactions between (1), (2), (3) and audit topic; we do this in order to get unbiased estimators for the general effects of interventions accounting for possible interactive effects between the two trials on the intervention effects. Unadjusted and adjusted intra-cluster correlations (ICCs) and corresponding 95% confidence intervals will be presented. We will report the estimates and two-sided 97.5% confidence intervals for the two main effects from this model and also for the interactions between (1) and (2) and audit topic.

The same sensitivity analyses will be run on this model as with the separate models.

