### **16.3.6 Further secondary analyses**

Exploratory analyses will be conducted investigating mediators (e.g. fidelity: delivery, receipt and enactment) and moderators (e.g. trust size) of the main effects of the two feedback interventions in the surgical and haematological audits.

A number of exploratory sub-group analyses are planned which will be specified in detail in the SAP. These will include trust/health board and patient level factors such as trust size, TP involvement, surgical procedure and Haematological diagnosis.

Sensitivity analysis will be undertaken to investigate how contamination events, such as merging hospital trusts, might affect the size and direction of primary outcome measure.

Full details of all secondary analyses will be given in the Statistical Analysis Plan.

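### Trust size is defined both as transfusion volume and as a tertile of audit cases submitted, and the protocol then uses the one label for adjustment, moderation and subgroups

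*Protocol*

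**What the plan says.** The Trial Summary (section 3) describes randomisation "with stratification for size (volume of blood transfusions) and region (Regional Transfusion Committee"), and section 5.3 repeats this. Section 13.2.1 lists, among the screening data that the National Comparative Audit (NCA) supplies for all UK trusts and health boards, "Trust and Health Board size (defined by volume of blood transfusions) to inform the stratification of the randomisation and the planned moderator analysis".

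Section 9 is the only place that says how size is scored. There, the rule given under the trust-size label reads: "For each audit we will review the number of cases submitted to baseline audit per cluster and then break these down into tertiles (Large, Medium", plus Small. The cut is made afresh for each audit, after baseline data collection has closed.

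The label then recurs without a definition:
- Section 16.3.4 fits the primary model "adjusting for design factors (that is, trust size, regional transfusion committee, and trust-level proportion of unnecessary transfusions at baseline").
- Section 16.3.5 carries the same covariates into the trust-level volume and Serious Hazards of Transfusion (SHOT) incident outcomes.
- Section 16.3.6 plans exploratory work on "moderators (e.g. trust size) of the main effects of the two feedback interventions" and, for the subgroup analyses, states: "These will include trust/health board and patient level factors such as trust size, TP involvement, surgical procedure and Haematological diagnosis".

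**The concern.** The two definitions measure different things. Screening volume is a property of the whole trust. The section 9 count covers one specialty over a registration window of three months (surgery) or one and a half months (haematology). It depends on which cases are registered and submitted, and section 8.3 provides for a process that manages how many cases each site audits. A trust can be Small in one trial and Large in the other.

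Because the label is shared, an analyst could take either variable and still follow the text. Two results are exposed. The first is the moderator and subgroup analysis: if it used the audit-case tertile, it would be reported as an effect of trust size while measuring topic caseload and submission. The second is the set of trust-level secondary outcomes in section 16.1.2. Most of these are totals over all specialities, so how well the covariates capture the scale of the trust bears directly on precision.

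**Working it through.** **1. Does the definition of size enter the sample size?** Inputs from section 16.2: arm rates 20/14/14/10%, two-sided alpha 0.025, power 80%, intraclass correlation 0.05, mean cluster size 45 with range 17 to 68. The coefficient of variation (CV) of cluster size is not stated. I took 0.283 (range/4 divided by 45) or 0.327 (uniform over the range).

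- Main effect on the log-odds scale: d = ½[logit(0.20) − logit(0.10)] = 0.4055. The 14% arms cancel.
- Sum of 1/[p(1−p)] over the four arms: 33.97.
- Effective n per arm = (2.241 + 0.842)² × ¼ × 33.97 / 0.4055² = 491.
- Design effect = 1 + [(CV² + 1) × 45 − 1] × 0.05 = 3.38 (CV 0.283) or 3.44 (CV 0.327).
- Clusters = 4 × 491 × design effect / 45 = about 148 or 150. Power at 152 clusters is 81.3% or 80.5%.

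The stated 152 is reproduced closely, and trust size appears nowhere in the calculation.

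**2. Which definition attaches to which use?**

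| Use | Section | Measure named there |
|---|---|---|
| Stratification (summary) | 3, 5.3 | Transfusion volume |
| Stratification and moderator (screening data) | 13.2.1 | Transfusion volume |
| Minimisation factor | 9 | Tertile of submitted audit cases |
| Primary-model covariate | 16.3.4 | Not stated; called a design factor |
| Trust-level outcome covariate | 16.3.5 | Same as primary model |
| Moderator and subgroup | 16.3.6 | Not stated |

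Sections 9 and 13.2.1 cannot both describe the randomisation. For the moderator, the only section that names a measure is 13.2.1, and it names volume.

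**3. How much would it matter if the tertile stood in for volume?** The protocol gives no correlation r between the measures, so r is an assumption. I treated the two (log) measures as bivariate normal, cut each into tertiles, and compared the classes. The share retained assumes a true effect that changes in equal steps from Small to Large volume. It is half the difference in mean volume class (coded 0, 1, 2) between the Large and Small audit-case tertiles.

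| r | Trusts changing class | Of 152 | Large-minus-small contrast retained |
|---|---|---|---|
| 0.7 | 42% | 63 | 59% |
| 0.8 | 35% | 53 | 69% |
| 0.9 | 26% | 39 | 80% |
| 0.95 | 18% | 28 | 86% |

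So for r from 0.7 to 0.95 the loss is 14% to 41%. At r = 1 nothing is lost.

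**4. The trust-level outcomes.** The stated covariates are trust size, regional committee and the baseline proportion of unnecessary transfusions. Only the first reflects how large the trust is, and section 16.3.5 states no exposure term. Under the same normal model, a tertile of log volume explains (2/3) × 1.091² = 79% of the variance of log volume, where 1.091 is the mean of the top third of a standard normal. A tertile of a measure correlated r with it explains 0.793 × r²: 39% at r = 0.7 and 72% at r = 0.95. The unexplained part is then 61% or 28%, against 21% for a volume tertile. Log volume entered as a continuous covariate leaves none of it.

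**The case against.** A reader might infer that many trusts are put in the wrong size class and that the moderator result is attenuated. The protocol supports neither statement.

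- No section scores the moderator from the audit-case tertile. Section 13.2.1 points to volume, and if that is followed there is no attenuation. Section 16.3.6 leaves the detail to the statistical analysis plan and labels the work exploratory.
- Calling a class wrong presumes that volume is the intended measure for minimisation. Section 9 may be a deliberate choice: its past-tense remark about the data supplied suggests that it records what was done, with the other sections left unrevised. The count is also a count of transfused patients, so it is not unrelated to volume, and differing by topic may be intended.
- The protocol gives no rate of incomplete baseline submission. It asks for registration of all consecutive cases and describes active chasing. The remark in section 16.3.1, "As a sizeable proportion of patients are expected to be missing from the main analyses", concerns the main analyses, not baseline submission by trust. A link between submission and engagement with feedback is conjecture.
- Sections 13.2.3 and 13.2.4 obtain pre-feedback Blood Stocks Management Scheme (BSMS) and SHOT data, which the analysis plan could use for adjustment.

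The first three points stand and limit the concern to the form given here. The fourth stands in part: those data will be held, but section 16.3.5 states the covariate set and does not include them. None of this removes the contradiction between sections 9 and 13.2.1, which the protocol itself must resolve.

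**Conclusion.** The contradiction is real, and it touches a minimisation factor, a covariate in every main model, and a named moderator and subgroup. It does not threaten the primary result. Both measures are available before allocation, so the minimisation is valid on either one. Adjusting the primary model for the factor actually used is appropriate, and the 152-cluster figure does not depend on it.

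The harm to the moderator analysis is conditional: mislabelling, and a loss of 14% to 41% of a large-minus-small contrast, arise only if the section 9 tertile is used. That range rests on an assumed correlation of 0.7 to 0.95 and on normality, neither of which comes from the protocol.

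For the trust-level outcomes the cost is precision, not bias. It applies most clearly to the totals over all specialities. It is less clear for preventable incidents within the targeted specialities, where topic caseload may itself be a relevant measure of scale.

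**What to change.** 1. In section 9, rename the minimisation factor 'baseline audit caseload (tertile)'. Keep that tertile in the primary model so that the analysis follows the randomisation, and make sections 3, 5.3, 13.2.1 and 16.3.4 agree with it.
2. In section 16.3.6, state that the trust-size moderator and subgroup use the screening transfusion volume of section 13.2.1, as that section already indicates.
3. In section 16.3.5, add log screening transfusion volume as a covariate for the trust-level BSMS and SHOT outcomes.

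The volume is already listed as screening data for all UK trusts and health boards, so no new collection or re-randomisation is needed. The cost is wording plus one extra covariate in the cluster-level models. Settling this before analysis also removes a later choice between two variables with the same name.

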## 10 Feedback-related interventions

Detailed protocols specifying the intended delivery of each component of the trial interventions will be written by the Intervention Leads (including [name], [name], [name] and [name]) and finalised following completion of Work Stream 1. The intervention protocols will not be disseminated to clinical audiences until the results of the two trials are in the public domain.

### 10.1 Usual feedback

Current practice is defined as the standard feedback delivered by the NCA following completion of an audit, targeting clinical teams within Trusts or Health Boards. Feedback is typically in the form of a written clinical audit report to hospital sites, a regional PowerPoint presentation and (often) action plan templates. The content of the written report varies, depending on the audit. How these clinical teams and organisations respond following receipt of the feedback is regarded as a consequence of the trial interventions – but is presently considered to be highly variable. We expect them to respond in the context of their clinical governance arrangements. No restrictions will be imposed on current practice or on Trusts or Health Boards undertaking additional development or training in the provision of feedback, with the exception that we will request that the staff who receive the feedback do not share with colleagues external to their own Trust or Health Board.

### 10.2 Enhanced feedback

The ‘enhanced’ feedback has been developed using the current evidence base for A&F  and behaviour change theory . While its proposed effects are theoretically plausible, there is real uncertainty regarding whether this will translate into improved outcomes. Equipose will be actively encouraged within the research team and the clinical community until the results of the trial are known.

*Enhanced feedback documents:* feedback documents with content written to specifically deliver behaviourally specified feedback and the relevant theoretically-consistent behaviour change techniques. These documents will be delivered as per usual practice by the NCA programme through written and graphic feedback presented in multiple feedback documents and presentations.

*Post-feedback support:* targeted dissemination of the feedback to relevant staff with discussion and agreement of action plans. The post-feedback support intervention comprises practical guidance for clinical teams on how to operationalise the process of responding to feedback, including materials for clinical teams to facilitate discussion and agreement of locally relevant goals and action plans based on feedback.

## 11 Definition of end of both trials

The end of trial is defined as the last clinical audit case collected at the time of follow-up of the Haematological audit.

## 12 Monitoring intervention adherence & fidelity

The AFFINITIE Programme includes a process evaluation to provide a detailed understanding of how the feedback interventions were delivered in practice and how staff responded to them. Specifically, the AFFINITIE process evaluation will be based on the Medical Research Council (MRC) guidance for conducting process evaluations of complex interventions. This guidance recommends assessing: i) the extent to which interventions are implemented by the intervention providers and enacted by intervention recipients as intended (i.e. with fidelity); ii) potential contextual influences on intervention implementation (e.g. publication of new transfusion guidelines, levels of available resources, staff); and iii) the extent to which degree of fidelity mediates intervention outcome. Specifically, the assessment of fidelity in the AFFINITIE program will also be based on a fidelity framework proposed by the NIH Behaviour Change Consortium (BCC) to investigate and report the extent to which the enhanced and standard feedback interventions were (i) designed, (ii) trained, (iii) delivered, (iv) received and (v) enacted as intended (i.e. with fidelity). Two linked process evaluations will be conducted alongside the two linked cluster randomised trials.

As part of the trial, the intervention developers and intervention providers will fully document their activities to provide a record of fidelity in terms of study design, provider training and intervention delivery (refer to section 13.5). This is necessary for monitoring the conduct of the trial but it will also be used to calculate estimates of the costs of the interventions and to inform analyses relating to mediators of the effect of randomised allocations on outcome.

Data collected from the Hospital Transfusion Teams for all clusters will be limited, including questionnaires to collect high-level data on contextual influences, the receipt and enactment of the interventions (e.g. confirmation of receipt of documentation and overall rating of the level of enactment of post-feedback support) (refer to section 13.5). These questionnaires will be sent to all hospitals approximately six months following intervention delivery.

Additional data will be collected for all Trusts randomised to receive Intervention 2 (i.e. enhanced post-feedback support). The post-feedback support intervention consists of two components: i) a web-based toolkit to support hospitals in planning their response to the feedback reports, including problem solving, goal setting, and action planning tools; and ii) telephone support sessions with a member(s) of the hospital transfusion team (e.g. transfusion practitioner) to promote engagement with, and facilitate use of, the web-based toolkit. In order to monitor the implementation of Intervention 2, all telephone support sessions will be audio-recorded to assess the extent to which the intervention providers delivered the telephone support with fidelity to the intervention manual. Informed verbal consent will be sought from the intervention recipient at the beginning of the call prior to commencing audio-recording; the telephone support session will not be audio-recorded if the intervention recipient does not provide informed consent. Quantitative web analytics data will also be collected on the extent to which intervention recipients engage with the web-based toolkit, including: number of log-ins, duration of log in, number of web pages viewed, and extent of completion of problem solving, action planning and goal-setting tools. This data will be collected automatically without additional input required from the intervention recipients. The web analytics data being collected will be clearly stated on the log-in page for the toolkit. Informed consent will be sought upon log-in to record this data, providing intervention recipients with the option to opt out of data collection.

All telephone support and web analytics data will be collected throughout the intervention delivery period, and cease upon collection of follow-up outcome data collection for each trial. At the point of data analysis, any identifying or personal information will be removed from the transcripts of the audio-recorded telephone support sessions and all web analytics data so that no individual clinical staff member or Trust may be identified directly from the data. Only AFFINITIE researchers will have access to the records and be able to re-identify the data (in the event of a participant requesting their data be removed from the programme). All data will be handled in accordance with the Data Protection Act 1998, and will be stored in secure locked cupboards, or on secure, password protected computers at City University. Data will be destroyed after a minimum of five years after the end of the trial, deleting all electronic files and shredding any documentation.

